## Methods and analysis

### Trial design

The study is a 24-week, two-arm, triple blinded randomized placebo-controlled trial evaluating the safety and effectiveness of the “PDNeuro” Helmet (see Figures 1, 2) compared with a sham helmet device. Treatment will consist of PBMt to the head six times per week for 12 weeks (see Figure 3), with Group 1 (the active group) receiving 12 min of infra-red and 12 min red LED, and Group 2 (the sham group) receiving sham treatment for 24 min. After the initial 12 weeks, the sham patients will be given the active treatment for 12 weeks while the active treatment group will have a 12 weeks washout period and then be re-assessed in 12 weeks (see Figure 3). Outcome measures will be collected by the study investigators that have received specialized training in assessment and data collection.

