##### UPDRS

The primary motor measure chosen is the motor assessment (Part 3) of the UPDRS as it is one of the most common movement assessment outcomes used in PD (Ivey et al., 2012), and demonstrates high internal consistency and inter-rater reliability while showing moderate construct validity (Rodriguez-Blazquez et al., 2017).

Furthermore, the UPDRS assessment has been shown to be clinically valid when conducted remotely (Schneider et al., 2020). Indeed, the feasibility, reliability and value of implementing remote telemedicine/video-based assessments for Parkinson’s disease patients for both research (Tarolli et al., 2020) and ongoing healthcare (Cubo et al., 2020) have been previously evaluated and deemed valid.

Sixteen of the eighteen items from the UPDRS motor were included. Rigidity was excluded as this is unable to be determined without manual assessment. As well, postural stability was not performed due to the potential risk of falling if performed without adequate supervision. In the UPDRS all items are scored on a scale from 0 (normal) to 4 (severe), and total scores obtained from the sum of the corresponding item scores, stage the severity of PD. These scores are to be collected using video link with attention being paid to positioning the camera and participant to ensure clear vision. The carer will be required to manipulate the camera to ensure that the participant is clearly visible. All assessors are trained in the administration of the UPDRS assessment tool to maximize the outcome measure.

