##### Carer’s diary

A carer’s diary can provide qualitative data on patient experiences, as well as note changes in clinical manifestations that are not observed in the clinical environment. This information in the areas of physical, cognitive, and emotional domains can reveal both positive and negative changes and may provide a more detailed picture of the effect of treatment.

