### Statistical analysis

This is a feasibility study trialing the efficacy of the “PDNeuro” Helmet transcranial device. The sample size of 40 participants falls within the recommendation of between 12 and 50 for feasibility clinical studies (Julious, 2005; Sim and Lewis, 2012). As a series of *N* = 1 studies, it is anticipated that only basic statistical analysis will be performed. For each outcome measure, descriptive data (mean, standard deviation) will be calculated. From this data, “minimally important difference” (MID) scores will be computed based on 1/2 SD of each measure. This is a common MID measure (Norman et al., 2003) based on the distribution of the participant scores at baseline and provides a sensitive indicator of significant change over time for *N* = 1 case studies. This has also been used with good effect in previous PBMt PD trials (Liebert et al., 2021). As such, it does not suffer from a lack of statistical power that would be evident with more traditional ANOVA approaches with small sample sizes. The number of participants showing improvement (i.e., difference between two time points > MID) can be compared between time points with chi-square analyses.

In total, 162 participants (81 + 81) were proposed for recruitment over a 2-year period. However, due to limitations involving in no small part to the substantial COVID-19 restrictions during the conception of this trial, the decision was made to reduce the total number of participants to 40, with the intention of increasing this by 122 at a later date.

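### The only responder rule counts improvement beyond the MID; it has no matching count of worsening and does not say which two time points it compares

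*Protocol article*

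**What the plan says.** The Statistical analysis section of the protocol article gives the whole quantitative plan in a few sentences.

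- Descriptive step: "For each outcome measure, descriptive data (mean, standard deviation) will be calculated".
- Threshold: MID "scores will be computed based on 1/2 SD of each measure", and this is "based on the distribution of the participant scores at baseline".
- Responder rule: "The number of participants showing improvement (i.e., difference between two time points > MID").
- Test: these counts "can be compared between time points with chi-square analyses".

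The same section presents the trial as a set of N = 1 studies. Outcomes are collected at baseline, week 12 and week 24 (Outcome measures). Under Trial design, the sham group then receives the active helmet, while "the active treatment group will have a 12 weeks washout period and then be re-assessed in 12 weeks". The abstract makes lasting improvement the main sign of efficacy. Under Carer's diary, the article says that this qualitative source "can reveal both positive and negative changes".

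**The concern.** The improver count is the only quantity that the article takes forward to a test, and it looks in one direction only. A participant who worsens by more than the MID has no category and falls in with those who barely moved. The article describes Parkinson's disease as progressive and builds in a washout, so decline beyond the MID is an outcome that the trial should expect to meet.

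Two conclusions are at stake. The first is whether the active helmet gives a net gain or a mixture of gains and losses. A count of improvers cannot tell these apart, because random variation and mixed effects both produce improvers. The second is whether any gain lasts. Group 1's week 24 assessment could answer that, but the rule does not say whether its week 24 difference is taken from baseline or from week 12. The two choices give very different pictures of the same loss.

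The stated test adds to the difficulty. It compares time points and not arms, so the sham group's rate of chance improvers is not set against the active group's count.

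**Working it through.** The article gives no expected responder rate, so there is no figure of its own to reproduce. The check is what its rule would count.

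**Inputs from the article.** MID = 0.5 baseline SD; assessments at 0, 12 and 24 weeks; 40 participants in two groups.

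**Assumptions, not in the article.** Normal scores; equal SD at each visit; the same test-retest correlation r for each pair of visits, with r = 0.7, 0.8 or 0.9; the sizes of the shifts; and 20 per group where counts are given.

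**Formulas, in baseline-SD units, with a positive shift m meaning benefit.**
- SD of change: s = √(2(1 − r)) = 0.775, 0.632, 0.447.
- P(improved) = 1 − Φ((0.5 − m)/s).
- P(worsened) = 1 − Φ((0.5 + m)/s).

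**1. Inert device (m = 0).** 0.5/s = 0.645, 0.791, 1.118.

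**2. Mixed effect with zero mean** (half m = +0.5, half m = −0.5). P(improved) = 0.5 × 0.5 + 0.5 × (1 − Φ(1/s)), where 1 − Φ(1/s) = 0.098, 0.057, 0.013.

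| | r = 0.7 | r = 0.8 | r = 0.9 |
|---|---|---|---|
| Inert: improved | 25.9% | 21.5% | 13.2% |
| Inert: worsened, not counted | 25.9% | 21.5% | 13.2% |
| Mixed: improved | 29.9% | 27.8% | 25.6% |
| Mixed: worsened, not counted | 29.9% | 27.8% | 25.6% |
| Excess improvers, mixed over inert, per 20 | 0.8 | 1.3 | 2.5 |

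At r = 0.5 the improver rates are 30.9% (inert) and 32.9% (mixed), a gap of 2 points.

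**3. Net harm, r = 0.8** (40% shift by +0.75 SD, 60% by −0.75 SD). The mean change is 0.4 × 0.75 − 0.6 × 0.75 = −0.15 SD. Improved: 27.6%, which is above the inert 21.5%. Worsened and not counted: 40.2%.

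**4. Washout in Group 1** (gain of 0.5 SD at week 12, fully lost by week 24).

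| | r = 0.7 | r = 0.8 | r = 0.9 |
|---|---|---|---|
| Improved, 0 to 12 | 50% | 50% | 50% |
| Improved, 0 to 24 | 25.9% | 21.5% | 13.2% |
| Improved, 12 to 24 | 9.8% | 5.7% | 1.3% |
| Worsened, 12 to 24, not counted | 50% | 50% | 50% |

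With baseline as reference, the loss shows indirectly as fewer improvers. With week 12 as reference, about 10 of 20 decline beyond the MID and no responder count records it.

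**The case against.** Several points on the other side are sound.

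- **Direction.** A reader might infer that, because the formula carries no sign, a rise on the motor score would be labelled improvement. The article does not support that. The word improvement governs the parenthesis, and the UPDRS section says that "In the UPDRS all items are scored on a scale from 0 (normal) to 4 (severe"), so a rise there cannot be an improvement. What is left is smaller: the scales run in different directions (for writing, smaller is the sign of disease), and the article does not state the direction scale by scale. An analysis plan that is not shown could do so.
- **Other sources of evidence.** A reader might infer that worsening appears in no quantitative result. That is too strong. Means and SDs are planned for every outcome, and in the zero-mean example they would show no average change beside the improver count. Safety is a separate primary outcome with weekly meetings and an adverse event committee, and does not depend on the MID rule. Still, means do not show how many individuals declined, and individual change is what an N = 1 framing asks about.
- **Washout.** Loss is visible if week 24 is compared with baseline. This stands, but the article does not commit to that reference.
- **Claim of efficacy.** A reader might infer that the plan would declare a mixed or null effect a success. The article sets no success threshold, and with an inert device a comparison of 0-12 with 0-24 improver counts is not biased towards significance. The risk lies in how a bare improver count is read.
- **Size.** The half-and-half split is illustrative, and its excess is only 4 points at r = 0.7.

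**Conclusion.** The point holds in limited form. The stated responder rule is one-sided. It pools participants who worsen beyond the MID with those unchanged, and it leaves the interval open. Group 1's loss of benefit in washout is therefore either missed by the responder counts (week 12 as reference) or seen only as a fall in improvers (baseline as reference).

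Over r = 0.7 to 0.9, chance alone makes 25.9% down to 13.2% of participants improvers, about 5.2 down to 2.6 per 20, with an equal number worsened and uncounted. The extra improvers from a zero-mean mixed effect are modest: 0.8 to 2.5 per 20, and about double the inert rate only at r = 0.9. All these figures rest on the assumed normality, correlations and shifts. The absence of a worsened category does not; it follows from the rule as written.

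**What to change.** In the Statistical analysis section, replace the improver rule with a three-way classification of each participant on each scale: improved by more than the MID, worsened by more than the MID, or unchanged. State the beneficial direction for every scale. Name the intervals: 0-12, 12-24 and 0-24 weeks. Report all three counts by randomised group, and compare the arms at week 12. Report Group 1's worsened count for weeks 12-24 as the washout result.

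This needs no new data or visits. It costs a few sentences and one more table column. The drawback for the sponsor is that improved minus worsened may look less favourable than improvers alone.

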**Methods and analysis:**

This is a 24-week, two-arm, triple-blinded randomized placebo-controlled clinical trial of a novel transcranial “PDNeuro” LED Helmet, comparing an active helmet to a sham helmet device. In a survey, 40 PD participants with Hoehn and Yahr Stage I–III during ON periods will be enrolled and randomly assigned into two groups. Both groups will be monitored weekly for the safety and tolerability of the “PDNeuro” LED Helmet. Clinical signs and symptoms assessed will include mobility, fine motor skills and cognition, with data collected at baseline, 12 weeks, and 24 weeks. Assessment tools include the TUG, UPDRS, and MoCA all validated for use in PD patients. Patient’s adherence to the device usage and participant drop out will be monitored weekly. At 12 weeks both placebo and treatment groups will crossover and placebo participants offered the treatment. The main indicator for clinical efficacy of the “PDneuro” Helmet is evidence of sustained improvements in motor and non-motor symptoms obtained from participant self-reported changes, carer reporting of changes and objective reassessment by the investigators. The outcomes will assist in a future larger randomized trial design.

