### Advantages and limitations

This is a triple blinded RCT designed to minimize bias and maximize the validity of any differences observed between the treatment and sham groups. While the triple blinding of this RCT is an advantage, restrictions resulting from SARS-CoV-2 affected the initial protocol, creating several limitations. Due to restrictions in Australia during the conception of this trial, it was not feasible to invite participants into a clinic setting for in-person intervention and assessments due to government regulations at the time. Furthermore, the increasing rate of infections and hospitalizations during this period meant that movement of research staff and participants to and from a clinic/hospital location would introduce an increased risk of potential COVID-19 infection. Therefore, the decision was made to pivot the study to a home-based trial to minimize as much person-to-person contact as possible, and to mitigate any risk of infection to our vulnerable population.

The scientific/clinical validity and feasibility of conducting our RCT remotely had been assessed prior to commencement of the study. For example, the UPDRS assessment used for the RCT has been shown to be clinically valid when conducted remotely (Schneider et al., 2020). Indeed, the feasibility, reliability, and value of implementing remote telemedicine/video-based assessments for Parkinson’s disease patients for both research (Tarolli et al., 2020) and ongoing healthcare (Cubo et al., 2020) have been previously evaluated and deemed valid. Furthermore, all outcome measures will be assessed by medical professionals (physicians, nurses, physiotherapists) who have been trained to conduct clinical assessments in Parkinson’s disease patients, with supervision of leading neurologist to ensure assessment accuracy and reliability.

The resulting limitation is that treatment is delivered unsupervised with only a carer present. This means that there is a reliance of self-reporting and participant honesty that the “PDNeuro” Helmet is being applied correctly for the duration of the treatment period. Assessments are also being recorded *via* video communication and although cameras are effective in providing visual feedback it is possible that fine tremors may be missed and reliance of carers to manipulate the camera and give good visual observation may present a challenge.

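### The only inferential test the protocol states compares improvers between time points with an ordinary chi-square; no active-versus-sham test or estimate is specified for this randomised sham-controlled trial.

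*Protocol article*

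**What the plan says.** The design is comparative. The Abstract describes the trial as "comparing an active helmet to a sham helmet device". Trial design calls it a "two-arm, triple blinded randomized placebo-controlled trial evaluating the safety and effectiveness" of the helmet. Advantages and limitations says it is "designed to minimize bias and maximize the validity of any differences observed between the treatment and sham groups".

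The Statistical analysis section takes another line. It frames the trial as a set of single-patient (N = 1) studies and says "it is anticipated that only basic statistical analysis will be performed". It plans means and standard deviations, and minimally important difference (MID) "scores will be computed based on 1/2 SD of each measure", taken from the baseline distribution. An improver is a participant whose change between two visits exceeds the MID. The number of improvers "can be compared between time points with chi-square analyses". The section adds that this approach avoids the lack of power that ANOVA would show in a small sample.

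No other section supplies an arm comparison. The sub-analysis by gender (Randomization) names neither a test nor an arm contrast. Assessments are at baseline, week 12 and week 24. In weeks 12 to 24 the sham group receives the active helmet and the active group has a washout.

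**The concern.** The secondary hypothesis is that the treatment attenuates motor and non-motor symptoms, and two of the three listed primary outcomes (modified MDS-UPDRS Part 3 and PDQ-39) measure symptoms or their impact. Only the concurrent sham group separates a device effect from whatever else changes over 12 weeks in people who wear a helmet, have weekly contact and repeat the same tests. The stated test does not make that separation.

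The schedule makes this worse. In the active group, weeks 0-12 are helmet weeks and weeks 12-24 are washout, so a placebo response that fades once the helmet is returned looks like a treatment effect that wears off. In the sham group the order is sham then active, and a placebo response that persists can count against the device.

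The test also does not fit the data. Pearson's chi-square assumes independent samples. Here the same participants supply both counts, and the two change scores share an assessment: week 12 (0-12 v 12-24) or baseline (0-12 v 0-24).

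**Working it through.** **The plan's own figures.** There is no power calculation to reproduce: no alpha, power, effect size or SD is given. The stated numbers agree with each other: 81 + 81 = 162, 162 − 40 = 122, and 40 lies between 12 and 50.

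**Inputs.** From the protocol: 40 participants in two groups, three visits, threshold of half the baseline SD, chi-square on improvers between time points. Assumed: 20 per arm, reliability (correlation between visits) r = 0.7 or 0.8, placebo response of 0.25 or 0.5 SD, no device effect, normal scores, no continuity correction, two-sided 5%.

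**Step 1: chance of being an improver.** The SD of a change score is √(2(1 − r)): 0.775 at r = 0.7 and 0.632 at r = 0.8, in baseline SD units. With mean improvement δ, P(improve) = 1 − Φ((0.5 − δ)/SD of change).

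| Mean improvement over the interval | r = 0.7 | r = 0.8 |
|---|---|---|
| 0.5 SD | 50% | 50% |
| 0 | 26% | 21.5% |
| −0.5 SD (response lost) | 10% | 6% |

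With no device effect, a 0.5 SD response that fades therefore gives about 50% improvers in weeks 0-12 against 6% to 10% in weeks 12-24.

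**Step 2: rejection rate of the time-point chi-square in one arm of 20** (40,000 simulated arms per setting).

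| Scenario, no device effect | Intervals | r = 0.7 | r = 0.8 |
|---|---|---|---|
| No change at all | 0-12 v 12-24 | 8% | 7% |
| No change at all | 0-12 v 0-24 | 2% | 2% |
| 0.25 SD, fades | 0-12 v 12-24 | 34% | 42-43% |
| 0.25 SD, fades | 0-12 v 0-24 | 8% | 11% |
| 0.5 SD, fades | 0-12 v 12-24 | 82% | 91% |
| 0.5 SD, fades | 0-12 v 0-24 | 32% | 47% |
| 0.5 SD, persists | 0-12 v 12-24 | 37% | 48-49% |
| 0.5 SD, persists | 0-12 v 0-24 | about 1.5% | about 1.5% |

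The first two rows show the pairing error. A shared week-12 score makes the two counts negatively related and the test too liberal. A shared baseline makes them positively related and the test too conservative.

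**Step 3: direction.** In the 0-12 v 12-24 rows with a placebo response, nearly all rejections favour weeks 0-12. In the active-then-washout arm those are the helmet weeks, so the result reads as efficacy. In the sham-then-active arm they are the sham weeks: with a persistent 0.5 SD response, about 50% improve on sham against 21.5% to 26% on the active helmet, which reads against the device.

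**Step 4: the randomised contrast under the same conditions.** With a placebo response of 0 to 0.75 SD shared by both arms during weeks 0-12 and r from 0.7 to 0.9, comparing arms at week 12 rejects in 3.8% to 5.6% of trials (chi-square on improvers) and 4.2% to 5.5% (t-test on change); 3,000 runs per setting.

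**Step 5: power of that contrast.** Power ≈ Φ(d√(n/2) − 1.96) with n = 20 per arm. For d = 0.5: Φ(1.58 − 1.96) = 35%. For d = 0.8: Φ(2.53 − 1.96) = 72%.

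**The case against.** - **The contrast may still be made.** A reader might infer that active and sham will never be compared. The document does not show that. The wording on the chi-square is permissive, the statistical analysis plan is not at hand, and the intent to compare arms is plain in the Abstract, Trial design and Advantages and limitations. What stands is narrower: the one test the article names is not the randomised contrast, and it is defended on grounds of power. Replacing a controlled comparison with a time-point comparison changes the question; it does not cure a power problem.
- **The sham arm is not ignored.** A reader might infer that the stated test leaves out the sham data. In the sham-then-active arm it compares a sham period with an active period in the same people. That uses sham data, but it is confounded with order and is not randomised.
- **Placebo response does not always favour the device.** A reader might infer that it would always be read as efficacy. Step 3 shows that it depends on the arm and on whether the response persists.
- **The sizes rest on assumptions.** The text does not say which intervals are compared or whether arms are separate or pooled. Across the placebo settings shown, the rate runs from about 1.5% to 91%. This limits the figures, not the structural defect.
- **This is a feasibility study with safety as its primary hypothesis.** True, and it bears on how firmly any efficacy result is read. But the same section describes the study as trialling efficacy, and two primary outcomes are efficacy measures.

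**Conclusion.** Wrong as written. The only stated inferential test is a within-participant comparison over time, carried out as if the counts were independent, and no active-versus-sham test or estimate is specified. Followed as it stands, it cannot answer the secondary hypothesis, although the data that could answer it are collected.

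That conclusion needs no assumed figures. The size does: with 20 per arm and reliability 0.7 to 0.8, null size is about 7% to 8% (0-12 v 12-24) or 2% (0-12 v 0-24). With a fading placebo response of 0.25 to 0.5 SD, false-positive rates in one arm run from about 34% to 91% for 0-12 v 12-24 and from about 8% to 47% for 0-12 v 0-24. The bias is towards efficacy in the active-then-washout arm if the response fades, and possibly against the device in the sham-then-active arm if it persists.

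**What to change.** In the Statistical analysis section:

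- State that efficacy is assessed by the active-minus-sham difference at week 12, adjusted for baseline score, in all randomised participants as allocated, with a 95% confidence interval.
- Apply this to both efficacy primary outcomes (modified MDS-UPDRS Part 3 and PDQ-39), without promoting one over the other, and likewise to the quantitative secondary outcomes.
- If responder counts are kept, compare them between arms at week 12.
- Label within-arm time-point comparisons descriptive, or test them with a paired method such as McNemar's test.
- Delete the N = 1 framing.

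The cost is rewording; no patients, visits or data are added. The small downside is modest power at 20 per arm (assumed): about 35% for d = 0.5 and 72% for d = 0.8. The estimate and its interval should therefore lead, read as feasibility-stage evidence for the larger trial.

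### The only test the Statistical analysis section names compares time points; it names no active-versus-sham contrast, which is the purpose of the randomised design

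*Protocol article*

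**What the plan says.** The design text is comparative. Trial design evaluates the helmet "compared with a sham helmet device", the abstract says the same, and Advantages and limitations says the design serves to "maximize the validity of any differences observed between the treatment and sham groups".

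The Statistical analysis section takes another course. It treats the trial as a set of N = 1 studies and says that "it is anticipated that only basic statistical analysis will be performed". Three elements follow:

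- Means and SDs for each outcome.
- A minimally important difference (MID): "scores will be computed based on 1/2 SD of each measure", taken from the baseline distribution.
- One test: "The number of participants showing improvement (i.e., difference between two time points > MID") "can be compared between time points with chi-square analyses".

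Of the MID approach it adds that "it does not suffer from a lack of statistical power that would be evident with more traditional ANOVA approaches with small sample sizes". No section names an active-versus-sham test, estimate or interval. Randomization adds only a sub-analysis by gender. The efficacy indicator in the abstract is sustained improvement, with no reference to sham.

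**The concern.** A sham arm exists so that change on active treatment can be set against the change that would have occurred anyway. A comparison between time points does not do that. Improvement from expectation, from learning the assessments or from ordinary fluctuation enters the improver count exactly as a device effect would.

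This is separate from the fact that an ordinary chi-square is unsuited to repeated counts on the same people. A correct paired test would still be testing the wrong contrast.

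At stake is the secondary hypothesis, that treatment attenuates symptoms. The two outcomes that carry it, modified MDS-UPDRS Part 3 and PDQ-39, are listed as primary outcomes. Only baseline to week 12 gives a randomised comparison of active with sham, because after that Group 1 goes to washout and Group 2 to active treatment.

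**Working it through.** **The plan's own figures.** The section's arithmetic is consistent: 81 + 81 = 162, 162 − 40 = 122, and 40 lies within 12 to 50. No stated number is contradicted. The defect lies in the contrast.

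**Inputs.** From the article: 40 participants in two groups, visits at baseline, week 12 and week 24, and an MID of 0.5 baseline SD. Assumed, because the article gives none of them: 20 per arm, normal scores with SD 1, correlation between visits r from 0.6 to 0.85, a non-specific improvement m = 0.3 SD in both arms, and no device effect. All tests are uncorrected chi-squares at 5%.

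**Step 1: how many count as improved.** The SD of a change is √(2(1 − r)), so P(improved) = 1 − Φ((0.5 − m)/√(2(1 − r))).

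- r = 0.6: change SD 0.894; 0.2/0.894 = 0.224; P = 41%.
- r = 0.7: change SD 0.775; 0.2/0.775 = 0.258; P = 40%.
- r = 0.85: change SD 0.548; 0.2/0.548 = 0.365; P = 36%.

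These rates are the same in both arms. With no mean change at all (m = 0), the formula still gives 29%, 26% and 18%.

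**Step 2: the named test within Group 1.** The sentence can be read in two ways. If improvers in weeks 0-12 are compared with improvers in weeks 12-24, the second-period rate is 18% to 29% when the shift persists (mean change 0). When the shift fades (mean change −0.3), it is 1 − Φ(0.8/√(2(1 − r))), or about 7% to 19%. Both lie well below 36% to 41% although the device does nothing. Simulated rejection rates over r = 0.6 to 0.85 (simulation error about one percentage point):

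| Comparison, no device effect | Shift persists to week 24 | Shift fades by week 24 |
|---|---|---|
| Group 1: improvers 0-12 v improvers 12-24 | about 17-28% | about 38-62% |
| Group 1: improved from baseline at week 12 v at week 24 | about 2% | about 8-20% |
| Active v sham improvers at week 12 | about 5% | about 5% |

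**Step 3: counts pooled over both arms, week 12 v week 24 (improvement from baseline).** With r = 0.7 and a shared, persisting 0.3 SD shift, the test rejects in about 1-2% of trials if the device effect reverses fully in washout, whether that effect is 0.5 or 0.8 SD. If the effect persists, it rejects in about 16% at 0.5 SD and 44% at 0.8 SD. The pooled test is therefore blind to a device effect only if that effect reverses.

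**Step 4: what the randomised contrast offers at 20 per arm.** For a baseline-adjusted comparison, the 95% half-width is about t(0.975; 37) × √(1 − r²) × √(2/20), with a small allowance for estimating the slope. At r = 0.7 this is 2.026 × 0.714 × 0.316 = 0.457, or 0.46 SD with the allowance; the range is 0.34 to 0.52 SD over r = 0.85 to 0.6. Power is about 57% (47% to 82%) at 0.5 SD and 92% (86% to over 99%) at 0.8 SD. Comparing improver proportions is weaker: 20% v 40% has 28% power.

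**The case against.** **The wording is permissive.** The section anticipates basic analysis and says that counts can be compared. It does not exclude an arm comparison, and an analysis plan not shown may contain one. A reader might infer that the trial will never compare active with sham, or that its results will be misread. The article does not support that. It shows that no such comparison is named and that misreading is possible. What remains is more than missing detail: the section states its analytic frame, defends it against group methods on grounds of power, and so conflicts with the article's own design. It would need correcting even if another document adds the contrast.

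**Group 2 moves from sham to active.** A time-point comparison there does set active against sham within the same people, and the order of treatment is randomised. But it remains a within-group comparison, confounded with period, practice and expectation, so it does not replace the parallel comparison at week 12.

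**Pooling.** A reader might infer that pooling the arms always cancels the device effect. Step 3 shows that this needs full reversal in washout. The article does not say that counts are pooled, and its efficacy indicator is sustained improvement.

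**Dependence on assumptions.** The false-positive rates change with the reading of the sentence and with whether the shift lasts; under one combination the rate is only about 2%. This stands, and the figures are illustrations.

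**Feasibility trial.** Safety is the primary hypothesis. Yet efficacy is a main objective, and two efficacy measures are primary outcomes.

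**Conclusion.** The point holds as a conflict between the stated analysis and the stated design. The single test named uses time, not randomised group, and no active-versus-sham contrast appears. That conclusion needs no assumption about correlation or placebo response.

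The size of the consequence does need them. Under the assumed values, a device with no effect yields more than a third of participants improved in each arm. The false-positive rate of the time-point test within Group 1 runs from about 2% to about 62%, depending on how the sentence is read and whether the shift lasts, against about 5% for the between-arm comparison.

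The power rationale also fails. An MID is a threshold for individual change; once counts are tested, the test has its own power, which is low at 20 per arm. This should be corrected before the analysis is carried out.

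**What to change.** In the Statistical analysis section:

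1. State that the efficacy analysis of modified MDS-UPDRS Part 3 and PDQ-39 is active versus sham at week 12, as randomised, reported as a baseline-adjusted mean difference with 95% CI. ANCOVA is one suitable model; adjustment for sex is optional.
2. Compare the proportions exceeding the MID between arms at week 12, as supporting evidence.
3. Label time-point comparisons and week-24 data as descriptive.
4. Delete the description of the trial as a series of N = 1 studies and the claim that the MID approach avoids low power.

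The cost is wording only: no new visits, measurements or participants. The drawback is a wide interval, about ±0.46 SD at r = 0.7, which a feasibility trial can report as it stands and use in planning the larger trial.
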